### Protocol amendments

Any modifications to the protocol which may impact the conduct of the trial, potential benefit of patients or may affect patient safety, including changes of study objectives, trial design, participant population, sample sizes, trial procedures, statistical analyses, or significant administrative aspects will require a formal amendment to the protocol. Such amendments will be agreed upon by the research team and, if needed, approved by the local Research Ethics Board. Administrative changes of the protocol (e.g., minor corrections and/or clarifications) that have no effect on how the trial is conducted will be agreed upon by the research team and documented.

### Project timeline

Recruitment will run from November 2023 to May 2026. Data collection is expected to be completed in July 2027, with data analysis and synthesis conducted in the fall of 2027.

### Data analysis plan

#### Primary outcome

An intention-to-treat protocol will be used, and estimates will be reported with arithmetic means and 95% confidence intervals. The primary outcome (number of days with activity-limiting pain) will be analyzed similar to Eklund et al. (2018,2019) [17, 48]. The number of days with activity-limiting pain will be modeled using generalized estimating equations (GEE) linear regression, using appropriate correlation structure and robust variance estimator. Terms for study arm, time, and study arm by time interaction will be included. A term for MC candidate (yes or no) will be added to this model to investigate stratification and its relationship to outcomes further.

Following a previous study that conducted a similar analysis [16], cost-effectiveness will be investigated both from the health care and societal perspectives. In the health care perspective only costs directly associated with the intervention will be included whereas in the societal perspective all available costs, direct and indirect modeled production loss costs, will be used. Direct medical costs considered in the study are treatment costs (treatment fee) and time loss during treatment and travel (an average time for travel is estimated and added to an average patient visit time). Indirect costs, such as production loss, will be estimated using the human capital approach, where lost time is valued using the hourly wage [65]. Since the data collection is performed between 2023 and 2025, all costs will be adjusted for inflation using a 3 to 5% inflation rate, with the baseline year of the study as a base year [66] and calculated in CAD$. Intervention effectiveness will be estimated by the primary outcome “number of days with a bothersome spinal pain” and self-rated health (EQ5D) as a secondary outcome. The results will be reported as cost-effectiveness planes, cost acceptability curves, and incremental cost-effectiveness ratios (ICER) where the extra cost per extra unit of health effect will be estimated for days with bothersome pain and quality-adjusted life years (QALYs). No interim analyses are planned for this study.

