**Trial registration:**

ClinicalTrials.gov NCT05350254. Prospectively registered on April 22, 2022, last modified on December 08, 2023. The first patient was randomized into the study on December 21, 2023.

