### Data collection

The automated SMS track, via Twilio System, will be used to collect SMS, and REDCap will be used to collect electronic questionnaire data. Each participating clinician will complete an initial questionnaire (Questionnaire 0-clinician) to record their individual characteristics.

Upon Questionnaire 0-patient completion, participating patients will be automatically registered in the Twilio system, given a confidential study ID linked to the clinician from which they are receiving treatment, and automatically scheduled to receive 3 questions via SMS every 2 weeks for 12 months. The follow-up questionnaires (Questionnaire 1–4) will be automatically sent via e-mail to both participating patients and clinicians at 3 weeks, 3, 6, and 12 months, respectively.

Data collection will be monitored daily in real-time, and contact with participating patients and clinicians will ensure high response rates. Specifically, in case of email delivery notification from REDCap or identification of incomplete questionnaires, email reminders will be sent to participating patients and clinicians.

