## Trial status

Protocol version 1.0. The trial is ongoing, and participants (chiropractors and patients) are being recruited. Study recruitment started in November 2023 and is anticipated to continue until May 2026. Data collection is expected to be completed in July 2027.

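### The costing rules rest on a 2023–2025 window that the timeline contradicts, give an inflation range instead of one rate or index, and class patients' time as a direct medical cost

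*Protocol article*

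**What the plan says.** The costing rules stand in the Protocol article, Data analysis plan, under Primary outcome. The inflation rule is: "Since the data collection is performed between 2023 and 2025, all costs will be adjusted for inflation using a 3 to 5% inflation rate". The price base is the baseline year of the study, with no calendar year named, and amounts are in Canadian dollars.

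On dates, Project timeline says "Recruitment will run from November 2023 to May 2026" and "Data collection is expected to be completed in July 2027", with analysis in the fall of 2027. Trial status repeats that recruitment is "anticipated to continue until May 2026" and gives the same July 2027 end. Under Data collection, each patient is "automatically scheduled to receive 3 questions via SMS every 2 weeks for 12 months".

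On cost classes, the paragraph says: "Direct medical costs considered in the study are treatment costs (treatment fee) and time loss during treatment and travel". On perspectives: "In the health care perspective only costs directly associated with the intervention will be included". The societal perspective is defined as all available costs, both direct costs and modelled production losses, with lost time valued at the hourly wage.

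**The concern.** Three stated rules are faulty.

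- The window that justifies the inflation adjustment ends before recruitment does.
- The adjustment is a range, so two analysts following the plan can report different costs and different incremental cost-effectiveness ratios from the same data. Nothing in the text calls the range a sensitivity analysis.
- Patients' own time is listed next to the treatment fee as a direct medical cost. The two perspectives differ in that the societal one adds indirect costs, so the natural reading puts this time into the health care perspective as well.

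The Objectives section makes cost-effectiveness part of the primary aim, so these rules bear on a headline result. The third matters most for the comparison between arms, because the strategies may change the number of visits. The Background reports that, in two subgroups of the previous trial, maintenance care meant 1.5 and 3.9 more treatments than control.

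**Working it through.** **1. The plan's end date.** Last recruitment May 2026 + 12 months of follow-up = May 2027, which fits the stated July 2027. An end in 2025 cannot be derived from any other date in the article.

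**2. How much follow-up lies after 2025.** Assumptions: uniform accrual to 31 May 2026, 365 days of follow-up, no dropout. Accrual starts either on 1 November 2023 (942 days) or at the first randomization ("The first patient was randomized into the study on December 21, 2023"; 892 days).

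- Enrolled after 2025 (151 days): 151/942 = 16.0%; 151/892 = 16.9%.
- Still in follow-up after 2025 (enrolled after 31 December 2024, 516 days): 516/942 = 54.8%; 516/892 = 57.8%.
- Person-time after 2025: those enrolled in 2025 contribute half their follow-up on average, and later enrolees all of it. (365/2 + 151)/942 = 35.4%; 333.5/892 = 37.4%.
- Person-time in 2027: 16.0% × (75.5/365) = 3.3%; 16.9% × (75.5/365) = 3.5%.

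Costs need not follow person-time, because six visits fall in the first three weeks. If every cost fell at enrolment, the share after 2025 would still be 16–17%.

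**3. What the range leaves open.** Relative gap between the two ends after *y* years: (1.05/1.03)^y − 1, with 2023 as base year (assumed).

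| Cost year | y | Deflator at 3% | Deflator at 5% | Gap |
|---|---|---|---|---|
| 2024 | 1 | 0.971 | 0.952 | 1.9% |
| 2025 | 2 | 0.943 | 0.907 | 3.9% |
| 2026 | 3 | 0.915 | 0.864 | 5.9% |
| 2027 | 4 | 0.888 | 0.823 | 8.0% |

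If the base year were 2024, the 2027 gap would be the three-year figure, 5.9%.

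**4. Average over follow-up.** With accrual from 1 November 2023, the shares of person-time in 2023 to 2027 are 0.5%, 25.4%, 38.8%, 32.0% and 3.3%. Weighting the deflators by these shares gives 0.9395 at 3% and 0.9025 at 5%. 0.9395/0.9025 − 1 = 4.1%. With accrual from 21 December 2023 the result is 0.9376/0.8994 − 1 = 4.2%.

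**5. Patient time.** Let *f* be the fee per visit, *w* the value of treatment and travel time per visit, and Δ the difference in mean visits between arms. With patient time in the health care perspective, the visit-driven incremental cost is Δ(f + w). Without it, it is Δf. The ratio is 1 + w/f. The article gives neither *f* nor *w*, so no number can be put on this. The effect does not cancel between arms unless Δ = 0.

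**The case against.** **Late costs.** A reader might infer that costs after 2025 are left out. The text does not support that. The dates only give the reason for adjusting, the operative rule covers all costs, and visits are recorded at every follow-up to 12 months. The window misdescribes when costs accrue, but it drops none of them.

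**Size of the inflation effect.** The 8.0% gap applies only to 2027 costs, about 3.4% of person-time. The average gap is about 4%. Randomization is in small blocks within clinician, so the arms accrue concurrently and the rate rescales both nearly equally. It would not normally change the sign of the cost difference. This stands and limits the importance of the first two parts.

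**The range may have a purpose.** It could be sensitivity bounds or year-specific rates, and a source that we cannot see is cited for the adjustment. A condensed article may also leave costing detail to a fuller document. But the article does not leave the rate open: it states a range as the rule and gives it neither meaning.

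**Perspective.** No sentence says that the whole list of direct medical costs fills the health care perspective, which is limited to costs directly tied to the intervention. So the misplacement is the most natural reading and not an explicit statement. The label needs correcting either way.

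**Double counting.** Lost time is also valued at the wage under indirect costs, so a reader might infer that visit hours are counted twice in the societal analysis. The documents do not show this. Table 2 defines missed workdays and lost productivity as due to pain, which is a different quantity from time spent attending visits. Overlap is possible, and a sentence ruling it out is enough.

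**Conclusion.** The concern holds in three limited parts.

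- **Firm:** the 2023–2025 window contradicts the article's own timeline. About 35–37% of follow-up person-time lies after 2025 under uniform accrual with no dropout.
- **Firm:** a 3–5% range does not determine the adjusted cost. The choice within it moves costs by about 4% on average and by 8.0% for 2027 costs, with a 2023 base and costs spread as person-time. It mainly rescales the cost difference between arms.
- **Probable on the natural reading:** patient time enters the health care perspective and multiplies the visit-driven incremental cost there by 1 + w/f, a factor that the documents do not allow us to evaluate.

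These should be corrected because cost-effectiveness belongs to the primary aim. They do not touch the comparison of days with activity-limiting pain.

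**What to change.** In the cost-effectiveness paragraph:

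1. Change the data collection window to 2023–2027, in line with Project timeline and Trial status.
2. Name the calendar year meant by the baseline year. Convert each cost to that year with one named, published price index for the year in which the cost occurred. Analysis is planned for the fall of 2027, so observed price data can replace an assumed rate. Keep 3–5%, if wanted, only as a labelled sensitivity analysis.
3. Keep treatment fees in the health care perspective and place patients' treatment and travel time in the societal perspective only. Add one sentence stating that time spent on visits is counted once and not again within production loss.

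This changes analysis wording only and needs no new data. It is best done before anyone sees costs by arm.

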#### Secondary outcomes

The secondary outcomes will be analyzed and reported independently of the primary outcome. Missed workdays due to pain, loss of work productivity due to pain, pain intensity, global perceived change, self-reported activity limitation, self-rated health, and pain self-efficacy will be reported with arithmetic means and 95% confidence intervals, and GEE linear regression models will be used.

Qualitative interviews data will be analyzed using interpretive description. An inductive approach to thematic analysis will be used to facilitate coding of the data driven by the responses rather than preconceived theoretical or analytical knowledge. Transcripts will be coded, and key themes will be identified. Several well-established techniques to ensure methodological rigor and trustworthiness for interpretive description will be used, including member checking (participants’ comments on any developed themes), verification (researchers converge on recognizing “identical patterns” in the data), referential adequacy (providing enough quotes to ensure the findings fit the data), maintaining an audit trail (records of decisions made), and maintaining a reflexive journal (to help the interviewers identify how their experience may influence the study results).

The RE-AIM framework will be used to assess the impact and implementation of the MAINTAIN instrument using other qualitative and quantitative analyses, see Appendix 1 summary table.

### Ethical considerations

This study has ethics approval from the Canadian Memorial Chiropractic College’s Research Ethics Board (Approval #: 2203B02). Written informed consent will be obtained from all participants prior to study entry. The informed consent document includes information regarding the potential use of de-identified data beyond the specific objectives of this study.

### Dissemination plans

The results from this trial will be disseminated regardless of the magnitude or direction of effect. Results from this trial will be submitted for publication in peer-reviewed journals and presented at national and international conferences related to chiropractic care (e.g., World Federation of Chiropractic Research Conference). Peer-review publications will be reported following CONSORT guidelines (including CONSORT-Harms extension) and TIDieR checklist. An infographic summary of our results will be developed and disseminated to all Canadian provincial chiropractic associations to be distributed to their respective members. This summary will also be distributed to students, faculty, and staff of the investigators’ institutions. Trial participants who are interested in receiving a summary of study results will also receive the study infographic via mail.

## Discussion

Although spinal pain has been a leading cause of disability and a healthcare challenge for many years, effective preventive strategies for recurrent episodes and deterioration for those who need it remain scarce. Previous trials found that people with persistent and recurrent low back pain in the Dysfunctional sub-group (based on the MPI) report better outcomes when receiving a MC approach [17, 48]. However, the MPI was not designed to be used in clinical practice, which led to the development of the MAINTAIN instrument specifically to identify patients who would most benefit from a MC approach in clinical practice [49].

A key benefit of having a brief instrument, such as the MAINTAIN instrument, is that it can be employed during the clinical encounter. The simple scoring algorithm allows clinicians to immediately use its results, providing an overview of the psychological aspects of patients’ pain experience. This can also inform clinicians’ follow-up questions targeted to specific domains. Additionally, MAINTAIN instrument scores can be used to help establish treatment goals tailored to each patient’s needs and preferences, thereby better aligning the management plan with a patient-centered approach.

If this trial is successful, the MAINTAIN instrument may contribute to reducing healthcare costs by identifying patients who would benefit from a MC approach, leading to more effective management of these patients. Spinal pain significantly impacts individuals, the healthcare system, and society [2–4], resulting in diminished quality of life, increased disability, lost productivity, and substantial healthcare expenses. Therefore, developing and implementing effective preventive strategies for targeted populations is imperative as it can significantly improve individual health, well-being, and quality of life.

By using a pragmatic design, the results of this trial will reflect real-world clinical practice. Additionally, the findings can be readily translated into practice and will provide a comprehensive understanding of the barriers and facilitators associated with the implementation of the MAINTAIN instrument in clinical practice. This, in turn, will be highly relevant to assessing whether this instrument should be recommended and implemented in clinical practice.

## Trial status

Protocol version 1.0. The trial is ongoing, and participants (chiropractors and patients) are being recruited. Study recruitment started in November 2023 and is anticipated to continue until May 2026. Data collection is expected to be completed in July 2027.

## Data Availability

Primary analysis of data will be conducted by the team biostatistician ([name]). Other members of the research team will also have access to de-identified data to perform the analysis of secondary outcomes, such as qualitative interviews and implementation assessment. Access to the participant-level dataset will be based on the established collaboration agreements including data transfer agreements.

## Appendix 1

**Table 3 Tab3:** Summary of outcomes, measures, and analysis plan using the RE-AIM framework

RE-AIM element	Outcome measure; source	Data collection time point; data analysis
**Reach** *The reach of the intervention into the target population*		
Interest	Number of participants enrolled in the study across all sites (chiropractic clinics) until last participating patient completes follow-up; study records	End of last follow-up; descriptive statistics
Recruitment	Proportion of eligible patients who consent and enroll compared to those that are invited but decline to participate	End of recruitment; proportions
Use of qualitative methods to understand reach/recruitment	Qualitative interview with chiropractors and patients	Qualitative description
**Effectiveness** *Positive and adverse effects of the intervention*		
Measure of primary outcomes	number of days with activity limiting pain; self-report	Bi-weekly; GEE linear regression
Measure of secondary outcomes	Self report: Pain intensity (NRS) Disability (NDI/RMDQ) Health related QOL (EQ-5D-5L) Self-efficacy (pain self-efficacy) Physical activity (IPAQ)	T_0_, T_1_ T_2_, T_3_, T_4_; GEE linear regression
Effectiveness perspectives	Qualitative interviews with patients and chiropractors	End of study participation: interpretative description
**Adoption** *Representation of setting and intervention agents who are willing to initiate and actively participate in program*		
Setting level		
Number of sites involved in the study	Number of chiropractors and clinics participating	T_4_; descriptive statistics
Characteristics of chiropractors	Characteristics of chiropractors	T_4_, descriptive statistics
**Implementation** *Fidelity to the intervention and adaptions*		
Assessment of patient’s symptoms	Implementation questionnaire: “Did you consider if the patient had more or less than 30 days with pain during the past 12 months? Yes/No” Implementation questionnaire: “Did you consider the patient’s GPE? Yes/No”	T_1_ T_2_, T_3_, T_4_; descriptive statistics
Use of MAINTAIN instrument	Implementation questionnaire: Did you consider the MAINTAIN score?	T_1_ T_2_, T_3_, T_4_; descriptive statistics
Assessment of progress towards the goals set in the treatment plan	Implementation questionnaire: Did you assess progress towards the patient-specific functional goals set during the previous visits?	T_1_ T_2_, T_3_, T_4_; descriptive statistics
Exercise prescription	Implementation questionnaire: Did you give the Graded Activity plan to the patient?	T_1_; descriptive statistics
Exercise compliance	Implementation questionnaire: Did you assess exercise compliance? Yes/No	T_2_, T_3_, T_4_; descriptive statistics
Number of sessions	Questionnaires: number of sessions attended per participant Number of maintenance care appointments per group Number of symptom-based care appointments per group	T_4_; descriptive statistics T_4_; descriptive statistics, negative binomial regression T_4_; descriptive statistics, negative binomial regression
Practice change	Qualitative interviews with chiropractors and patients	End of study participation: Interpretative description
**Maintenance** *Extent to which program becomes sustained over time*		
Practice change	Qualitative interviews with chiropractors	End of study participation: Interpretative description

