### Objectives

The overall goal of this randomized clinical trial is to investigate the impact and process of implementing the MAINTAIN instrument in clinical practice to classify patients with spinal pain. The primary aim of this study is to assess the effectiveness and cost-effectiveness of stratified MC guided by the MAINTAIN instrument score compared to standard chiropractic care (without the MAINTAIN instrument). The secondary aim is to assess the fidelity and procedure compliance of implementing the MAINTAIN instrument.

We hypothesize that participants receiving the stratified intervention guided by the MAINTAIN instrument will present better outcomes (e.g., fewer days with activity-limiting pain and lower pain intensity and disability) at 12-months compared to the standard chiropractic care intervention. It is also hypothesized that compliance with procedures to implement the MAINTAIN instrument will be high.

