### Randomization

Participants will be randomly allocated to one of the two intervention arms at the first visit, as part of Questionnaire 0-clinician (immediately after eligibility criteria confirmation): Stratified Maintenance Care (SMC) or Standard Chiropractic Care (SCC), with the number of individuals equally balanced between groups. Central randomization will be performed, using block randomization stratified by clinician, performed by the study biostatistician ([name]) using SAS software. To ensure the allocation sequence is concealed from the researchers and participating clinics, varying block sizes of 2, 4, and 6 will be used. The unique randomization orders will be uploaded into REDCap (Research Electronic Data Capture system, Vanderbilt University, Tennessee) [51]. Each chiropractor will indicate, in their Questionnaire 0-clinician, the number of the patient (i.e., first patient enrolled = #1; second patient enrolled = #2, etc.), which will reveal that patient's group allocation. Importantly, chiropractors will only have access to the MAINTAIN instrument score for patients allocated to the MC group.

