### Baseline and follow-up assessments

A summary of baseline and follow-up assessments is detailed in Table 2. Baseline data (Questionnaire 0) will be collected from both clinicians and patients at the first visit. Clinician data will include implementation data as well as their clinical impression of the patient. Patient data will be collected on demographics, current pain (numeric pain scale (NRS) [54]), pain in the past week (NRS), activity limitation/disability (neck disability index (NDI) [55]/Roland-Morris Disability Questionnaire (RMDQ) [56]), psychological and behavioral consequences of pain (MPI [57]), self-rated health (EQ-5D [58]), the MAINTAIN instrument [49], beliefs of patients on their ability to function with pain (pain self-efficacy questionnaire [59]), physical activity (International Physical Activity Questionnaire (IPAQ) [60]), and expectations of treatment.

Follow-up assessment (Questionnaire 1–4) will be completed at 3 weeks, 3 months, 6 months, and 12 months, also collecting data from clinicians and patients. Practitioners will provide data on implementation and clinical impression of the patient, as well as expectations of care if the patient is receiving MC (Yes/No), and the date and content of treatment visits. In addition to these questionnaires, patients will also receive an SMS every 2 weeks to collect data on activities limited due to pain in the last 0–14 days, missed working days due to pain, and loss of work productivity due to pain. Figure 2 presents the schedule of participating practitioners’ and patients’ enrollment, interventions, and assessments.

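### Table 3 lists no patient-level comparison of delivered care with the care the GPC and MAINTAIN rule assigns, so the fidelity aim rests on a 'considered' item and on appointment counts for an undefined group

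*Protocol article*

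**What the plan says.** The Objectives section states: "The secondary aim is to assess the fidelity and procedure compliance of implementing the MAINTAIN instrument". It adds an expectation: "It is also hypothesized that compliance with procedures to implement the MAINTAIN instrument will be high".

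The Interventions section (Stratified MC) defines what is to be followed. Patients with a GPC score of 5 at 3 weeks are responders. Responders scoring 22 or more on MAINTAIN are assigned to maintenance care (MC), and responders scoring 21 or less to symptom-guided care (SGC). Patients with a GPC score of 4 or less receive an alternative treatment chosen by the clinician. In explaining the higher cutoff, the section says that one group in this design has to follow its assigned intervention.

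Appendix 1, Table 3, lists the measures for the Implementation element, described as "Fidelity to the intervention and adaptions":

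- use of the instrument: "Implementation questionnaire: Did you consider the MAINTAIN score", at T1 to T4, with descriptive statistics;
- response to initial care: "Did you consider the patient’s GPE? Yes/No";
- sessions attended per participant, and numbers of MC and of symptom-based appointments per group, the last two also with negative binomial regression.

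Separately, under Baseline and follow-up assessments, clinicians report "if the patient is receiving MC (Yes/No), and the date and content of treatment visits".

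**The concern.** Fidelity to a deterministic rule means that the care a patient received is the care the rule assigned. The item on the MAINTAIN score records something weaker: that the chiropractor took the score into account. Someone who reads a score of 30 and does not offer MC, or reads a score of 10 and does, can answer yes without error. The respondent is also the unblinded treating clinician.

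The appointment counts do describe delivered care, but the article uses the word group both for the trial arms and for the care strata within the stratified arm. If the counts are by arm, they show how much MC was given but not whether it went to the patients the rule selected.

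What is at stake is the secondary aim and the reading of the primary result. In a hybrid effectiveness-implementation trial, a null result needs to be attributed either to a rule that does not help or to a rule that was not applied. The measures as listed may not separate the two.

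**Working it through.** The plan gives no figure for fidelity, so there is nothing to reproduce. The check asks whether the listed measures can look good while delivered care departs from the rule.

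**Inputs**

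- Stratified arm: the Sample size section aims for 220 patients, so 220 / 2 = 110.
- Share scoring 22 or more: one half. This is a proxy, because the Sample size section expects about half of each arm to be classified as dysfunctional.
- Share responding at 3 weeks, r: not given. Assumed 40%, 60% or 80%, equal in both score halves.
- c = share of MC-assigned patients who receive MC; w = share of SGC-assigned patients who receive MC. Both are hypothetical.

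**Formulas**

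- Assigned to MC: M = 110 × 0.5 × r. Assigned to SGC: S = 110 × 0.5 × r.
- MC recipients in the arm: M·c + S·w.
- Agreement among responders: (M·c + S·(1 − w)) / (M + S).

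For r = 40%, 60%, 80%, M = S = 22, 33, 44. Numbers are expected values, so fractions occur.

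| c | w | MC recipients in the arm (r = 40%, 60%, 80%) | Agreement |
|---|---|---|---|
| 1 | 0 | 22, 33, 44 | 100% |
| 0.5 | 0.5 | 22, 33, 44 | 50% |
| 0.5 | 0.2 | 15.4, 23.1, 30.8 | 65% |
| 0.5 | 0 | 11, 16.5, 22 | 75% |

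**Worked case** (r = 60%, c = 0.5, w = 0.5): recipients = 33 × 0.5 + 33 × 0.5 = 33; agreement = (16.5 + 16.5) / 66 = 50%.

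**Reading the table**

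1. The 'considered' item can be 100% yes in every row.
2. Counted by arm, the second row cannot be told from perfect adherence. The third and fourth rows show a shortfall.
3. Counted by assigned care group, all three departures show. In the second row with r = 60%, 16.5 of 33 MC-assigned patients receive MC where the rule implies 33, and 16.5 of 33 SGC-assigned patients receive it where the rule implies none.
4. More generally, with M = S the arm total is unchanged whenever c + w = 1, and agreement is then (c + 1 − w) / 2 = c. An unchanged arm total is therefore compatible with any agreement from 0% to 100%.

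Table 3 counts appointments rather than recipients. The cancellation carries over if the number of MC appointments per recipient is similar in the two care groups, which is a further assumption.

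**The case against.** The strongest reply is that delivered care is in the plan. Table 3 counts sessions and both kinds of appointment, clinicians record MC status, visit dates and visit content, the alternative treatment of non-responders is recorded, and the coordinator contacts chiropractors monthly about adherence (Study setting). Agreement can be derived from these data, and gross departures would be visible to anyone who looked. Table 3 is also a summary in a journal article, and the analysis plan is not shown. Much of this stands. It rules out saying that fidelity is measured by self-report alone, or that a null result could never be interpreted. It does not remove the point: Table 3 names a measure, a time point and an analysis for each row, none compares assigned with delivered care, and the one row on use of the instrument does not fit the stated aim.

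A second reply also stands in part. Delivered care mixes clinician fidelity with patient uptake, since MC is recommended and SGC patients return only when symptoms do. For non-responders almost any care fits the rule, so agreement is informative only among responders.

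Two stronger readings are tempting but not supported.

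- A reader might infer that "Did you consider if the patient had more or less than 30 days with pain during the past 12 months" is empty because eligibility already requires more than 30 days with pain. The item asks what the clinician considered, at T1 to T4. Eligibility fixes the patient's history, not that answer.
- A reader might infer from "chiropractors will only have access to the MAINTAIN instrument score for patients allocated to the MC group" that half of all answers to the MAINTAIN item must be no, capping it at 50%. That requires the item to be asked in the control arm and pooled over arms, and Table 3 states neither. If it is asked in both arms and reported by arm, a yes in the control arm could signal contamination.

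**Conclusion.** The point holds in a limited form. The listed fidelity outcomes contain no patient-level comparison of delivered with rule-assigned care, the 'considered' item can read 100% at any level of agreement, and the appointment counts are informative or not depending on an undefined word. If group means arm, agreement among responders can be 50%, and in the extreme 0%, with the arm's MC total unchanged. If it means assigned care group, these departures would show.

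The illustration rests on half the arm scoring 22 or more, equal response in both halves, and hypothetical departures. It shows what is possible and does not forecast adherence. The intention-to-treat estimate of the primary outcome is not affected. This is an inexpensive improvement to the secondary aim and to the interpretation of the trial, not a flaw in the main comparison.

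**What to change.** In Appendix 1, Table 3, under Implementation:

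- Add as the main fidelity outcome the proportion of stratified-arm responders (those assigned to MC or to SGC) whose recorded care matches the care group given by their GPC and MAINTAIN scores. Derive it from MC yes/no, visit dates and visit content, and report it by care group and by clinician.
- State which MAINTAIN assessment defines the assigned group, since Table 2 lists the instrument at the first visit and again at 3 weeks.
- Report non-responders separately and descriptively.
- Tabulate MC and symptom-based appointments by assigned care group as well as by arm.
- Keep the 'considered' items as supporting process data, reported by arm.

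The cost is one derived variable, with some work to define a match for each care group from the article's own description of it. No new data and no change to patient care are needed. The article reports the trial as ongoing, with data collection to July 2027 and no interim analyses, so this can still be specified in advance. There are three downsides. The figure will partly reflect patient uptake and should be labelled accordingly. MC status is itself reported by the clinician, so visit dates and content should be used to check it. The result will probably be lower than the self-reported one.
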